## Abstract

**Background:**

The management of type 2 diabetes mellitus (T2DM) remains a complex clinical challenge, particularly for patients requiring multiple daily insulin injections (MDI). Advances in precision medicine and continuous glucose monitoring (CGM) have created opportunities to personalize treatment and potentially reduce the therapeutic burden on people with T2DM. Assessing β cell function and autoimmunity could help identify patients with T2DM eligible for simplified regimens without compromising glycemic control.

**Objective:**

The aim of this study is to test a simple personalized medicine protocol in routine clinical practice for people with T2DM treated with MDI. The intervention is based on evaluating C-peptide and glutamic acid decarboxylase autoantibody status with the goal of improving diagnostic accuracy and optimizing treatment.

**Methods:**

This is a pragmatic before-and-after intervention study involving people with T2DM currently receiving MDI across primary care centers and a referral hospital in the Lleida health care region in Catalonia (Spain). Eligible participants will undergo clinical and laboratory assessment, including C-peptide and glutamic acid decarboxylase autoantibody testing, and wear a CGM device. On the basis of a predefined algorithm, patients may either continue or discontinue prandial insulin. The primary outcome is the proportion of patients in whom prandial insulin is discontinued and remains discontinued over 6 months. Secondary outcomes include changes in hemoglobin A_1c_, CGM metric variables, quality of life, adherence, and treatment satisfaction.

**Results:**

Recruitment was completed on March 31, 2025. The follow-up phase is ongoing and expected to conclude by September 30, 2025. Data analysis will begin thereafter.

**Conclusions:**

This study will evaluate the feasibility and impact of implementing a personalized therapeutic approach for persons with T2DM receiving MDI in real-world clinical settings. If effective, this strategy could contribute to safer, simpler, and more individualized diabetes care.

## Introduction

### Type 2 Diabetes Mellitus and Continuous Glucose Monitoring

Diabetes mellitus (DM) is considered a global pandemic with increasing incidence and prevalence and is expected to affect 853 million people worldwide by 2050 [1]. Type 2 DM (T2DM) is a chronic and progressive disease characterized by peripheral insulin resistance and a decline in β cell function [2,3]. The degree of insulin resistance and secretion, the rate of deterioration, the associated metabolic phenotype, the response to treatment, and the occurrence of chronic complications vary across individuals [4].

Although T2DM accounts for over 90% of diabetes cases worldwide [1], a significant proportion of patients diagnosed with T2DM may actually have other forms of diabetes. Among these, latent autoimmune diabetes in adults (LADA) is noteworthy. LADA, a slowly progressive form of autoimmune diabetes, is characterized by the presence of pancreatic autoantibodies and a faster progression to insulin dependence than is typically observed in T2DM [5]. It is often misdiagnosed due to reliance on the clinical phenotype alone [6]. The prevalence of LADA varies by population and geography, ranging from 3% to 12% of all persons with DM [7]. Diagnosis requires detection of at least one pancreatic autoantibody, with the most common being glutamic acid decarboxylase autoantibody (GADAb) [8].

Managing T2DM remains a significant clinical challenge as its progressive nature often increases treatment complexity over time. While approximately 10% of patients eventually require complex insulin regimens [9], newer pharmacological agents and individualized treatment strategies may allow for treatment simplification, reduction of hypoglycemia risk, and improvements in quality of life when aligned with personalized glycemic targets [10-13]. C-peptide measurement can be used to assess endogenous insulin production and serve as a proxy for residual β cell function. This information may help determine whether prandial insulin is necessary or could be safely discontinued in favor of alternative therapies [14].

A randomized controlled trial by Rosenstock et al [15] demonstrated that, in people with T2DM, discontinuing prandial insulin and initiating a once-weekly glucagonlike peptide-1 receptor agonist led to improved glycemic control approaching normoglycemia, reduced hypoglycemia, decreased body weight, and improved quality of life. Similarly, the BEYOND trial by Giugliano et al [16] evaluated switching from basal bolus insulin regimens to a glucagonlike peptide-1 receptor agonist or a sodium-glucose cotransporter type 2 inhibitor. Comparable glycemic control was achieved with lower total insulin doses, fewer daily injections, and reduced hypoglycemia, along with improved weight management and patient satisfaction. A comprehensive review by Giugliano et al [17] including these and other studies confirmed that insulin therapy can be simplified in persons with T2DM without compromising glycemic control while reducing treatment complexity, hypoglycemia risk, and polypharmacy.

Continuous glucose monitoring (CGM) has been evaluated in both randomized trials and real-world studies involving people with T2DM treated with multiple daily insulin injections (MDI), basal insulin, or noninsulin regimens [18,19]. In Catalonia (northeast Spain), the public implementation of CGM for people with T2DM on MDI was approved in November 2023. This required collaboration and coordination between different care providers, constituting an opportunity to develop and implement this protocol in routine clinical practice [20].

This project proposes implementing a precision medicine algorithm for persons with T2DM treated with MDI in real-world clinical practice. This algorithm incorporates assessment of pancreatic autoimmunity and residual β cell function (pancreatic reserve) into the decision-making workup.

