### Study Design and Settings

We designed a nonrandomized pragmatic intervention study targeting people diagnosed with T2DM who were treated with MDI. This before-and-after intervention was designed to assess the real-world applicability of a precision medicine algorithm. Rather than using a control group, this study uses each participant as their own control, comparing clinical outcomes before and after the intervention. The intervention was adapted to be integrated into routine clinical workflows across both primary and specialized care settings.

This study is being conducted within 21 primary health care centers of the Catalan Health Institute (Institut Català de la Salut) in the Lleida health care region (Catalonia, Spain; Multimedia Appendix 1) together with the Department of Endocrinology and Nutrition, University Hospital Arnau de Vilanova, as the reference tertiary center.

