### Eligibility Criteria

We included adults aged ≥18 years with a confirmed diagnosis of T2DM. To be enrolled in the study, participants must be on an MDI regimen, defined as receiving at least 2 doses of prandial insulin per day (either regular insulin or a rapid-acting insulin analogue) administered separately or as part of a fixed-dose combination.

We excluded individuals with a known diagnosis of diabetes other than T2DM, pregnant women, and those with severe cognitive impairment or any condition that prevented the use of CGM. We also excluded participants with current drug or alcohol abuse, those receiving systemic glucocorticoids for acute conditions at the time of inclusion, and individuals undergoing temporary insulin therapy expected to last less than 6 months.

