### Recruitment and Sampling Strategy

The participant selection sampling strategy was a convenient approach based on the availability and willingness to participate of the patients who fulfilled the study criteria [21].

Participating centers were selected based on geographic distribution and availability of primary health care teams. Teams received virtual training sessions. Sessions included information related to the background, objectives, protocol procedures, and data collection methods before participant recruitment. The study recruitment period lasted 6 months.

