### Study Procedures and Timeline

Potential participants were identified by local study physicians and nurses using the primary care eCAP (Catalan Health Institute) electronic clinical record software. Each participant underwent 4 study visits. Initially, a preselection visit was conducted through electronic health record review without direct patient contact. Eligible individuals were then contacted and provided with detailed study information. Those who agreed to participate were invited to the inclusion visit (visit 0), during which written informed consent was obtained by research staff. This visit involved a clinical interview, a physical examination, laboratory testing (including C-peptide and GADAb measurements), and the placement of a CGM device. All participants used CGM for 10 to 15 days prior to the intervention. Two weeks later, the first follow-up visit (visit 1) was conducted. At this visit, therapeutic decisions were made based on C-peptide and GADAb results, and treatment was adjusted according to the predefined therapeutic intervention algorithm (Figure 1).

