### Study Outcomes

We defined the primary study outcome as the proportion of participants in whom prandial insulin is successfully discontinued after the application of the therapeutic algorithm and who remain without prandial insulin at the final visit (6 months).

Secondary outcomes encompass several domains. Glycemic control following therapeutic optimization is evaluated through changes in HbA_1c_ and CGM-derived metrics, including time in range and time below range. Patient-reported outcomes are also assessed by comparing changes from baseline to 6 months after the intervention, including changes in quality of life (using the Diabetes Quality of Life Questionnaire), treatment satisfaction (using the Diabetes Treatment Satisfaction Questionnaire, both status and change versions), medication adherence (measured using the Adherence to Refills and Medications Scale), and physical activity levels (evaluated using the Spanish version of the International Physical Activity Questionnaire).

Safety outcomes include the number of severe hypoglycemic episodes at the final visit 6 months after the intervention compared with the 12-month period before enrollment. The study also examines the predictive value of CGM metrics by analyzing their association with pancreatic reserve and insulin resistance considering both continuous and categorical variables.

Finally, among patients who continue prandial insulin and CGM use for 6 months, the study assesses the impact of CGM on glycemic control (HbA_1c_ and CGM metrics), as well as changes in quality of life, treatment satisfaction, and medication adherence.

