## Results

Recruitment for the study began in January 2024 and was completed on March 31, 2025.

As of August 31, 2025, the study is in its final follow-up phase, scheduled to conclude on September 30, 2025. Formal data analysis will begin after completion of follow-up and final data collection.

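### Prior CGM use is neither excluded nor listed as recorded, so the continuers' CGM-impact analysis and the severe-hypoglycemia look-back have no assured CGM-free baseline

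*Protocol article*

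**What the plan says.** The Introduction (Type 2 Diabetes Mellitus and Continuous Glucose Monitoring) reports for Catalonia that "the public implementation of CGM for people with T2DM on MDI was approved in November 2023". The Results section says "Recruitment for the study began in January 2024 and was completed on March 31, 2025". Recruitment and Sampling Strategy says instead "The study recruitment period lasted 6 months".

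The only CGM-related exclusion in Eligibility Criteria covers "those with severe cognitive impairment or any condition that prevented the use of CGM". Past or current CGM use is not mentioned there, and Table 1 has no row for it. Multimedia Appendix 2, which defines the variables, is not shown. At visit 0 the procedures include "laboratory testing (including C-peptide and GADAb measurements), and the placement of a CGM device", and everyone then wears CGM for 10 to 15 days before the treatment decision.

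There is no control group: "this study uses each participant as their own control, comparing clinical outcomes before and after the intervention". Study Outcomes adds a specific CGM question: "among patients who continue prandial insulin and CGM use for 6 months, the study assesses the impact of CGM on glycemic control", together with quality of life, satisfaction and adherence. Severe hypoglycemia over the 6 study months is compared with the 12 months before enrolment. Sample Size and Statistical Analysis names paired t or Wilcoxon tests and linear mixed models, and states no restriction, stratum or covariate for prior CGM. Under Intervention Algorithm, people who stop prandial insulin typically stop CGM too.

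**The concern.** With each participant as their own control, an effect of CGM can be read from before-after change only if the before state is free of CGM. Funding for people on MDI was approved before the first participant was recruited, and nothing in the stated criteria keeps existing users out. A continuer who already had CGM has no CGM-naive baseline HbA1c, quality-of-life, satisfaction or adherence value, and that person's change says nothing about starting CGM.

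Two other comparisons are touched in different ways. The hypoglycemia look-back could contain some CGM-covered time, and the possible share rises with enrolment date. Among discontinuers, a prior user goes from established CGM to none, while other participants go from no CGM, through a short study wear, back to none. At stake is the interpretation of named secondary and safety results.

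**Working it through.** **1. The plan's own figure.** With p = 0.25, d = 0.05 and N = 1388, n0 = 1.96² × 0.25 × 0.75 / 0.05² = 288.1. With the finite population correction, n = 288.1 / (1 + 287.1/1388) = 238.7, rounded up to 239. This reproduces. The primary outcome is a proportion at 6 months with no before value, so prior CGM changes neither the estimate nor the sample size.

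**2. How much of the before period can follow approval.** Inputs are approval in November 2023 (taken as the 1st or the 30th) and enrolment from 1 January 2024 to 31 March 2025 (455 days). Even enrolment over the window is assumed. The article gives no roll-out or uptake data, so these are upper limits on exposure.

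- First participant: 61 or 32 days after approval, which is 17% or 9% of a 12-month look-back.
- Last participant: 16 to 17 months after approval, so the look-back can be fully covered.
- A 12-month look-back lies wholly after approval only for enrolment from 31 October (or 29 November) 2024. That is 151/455 = 33% or 122/455 = 27% of enrolment dates.
- A 3-month window behind baseline HbA1c (assumed) lies wholly after approval from 31 January (or 29 February) 2024. That is 425/455 = 93% or 396/455 = 87%.

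**3. The same check under the 6-month recruitment statement.** For 1 January to 30 June 2024 (181 days), the last participant enrols 242 or 213 days after approval, so 66% or 58% of the look-back can be covered. No look-back is fully covered. The 3-month HbA1c window is wholly after approval for 151/181 = 83% or 122/181 = 67% of dates. The HbA1c question therefore survives either reading, while the full-coverage figure for hypoglycemia does not.

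**4. Attenuation in continuers.** Let D be the true change from starting CGM and p the share of continuers already on CGM with no further effect. The expected estimate is (1-p) × D + p × 0 = (1-p) × D. Neither p nor D is in the article. For an assumed D of 0.3 HbA1c points:

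| p | Expected estimate | Power, SD 1.0 | Power, SD 1.5 |
|---|---|---|---|
| 0 | 0.300 | 98% | 76% |
| 25% | 0.225 | 85% | 52% |
| 50% | 0.150 | 52% | 27% |

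Power is the normal approximation for a paired test, Φ(estimate × √n / SD − 1.96). It uses n = 0.75 × 239 = 179 continuers, assuming that the planned 25% discontinue and that nobody is lost. The SDs are assumed.

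**5. Discontinuers.** If losing established CGM reverses its effect, prior users move the mean change against the intervention by p × D. For D = 0.3 to 0.4 and p = 25% to 50% (all assumed), that is 0.25 × 0.3 = 0.075 up to 0.5 × 0.4 = 0.2 points. This is a shift, not an attenuation.

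**The case against.** The strongest reply is that no prior user is documented. The article gives an approval date, not a roll-out date or an uptake figure. A device is placed at visit 0, Table 1 shows CGM data only from visit 1 onward, and the Introduction presents the approval as the opportunity for the project. All of this fits CGM beginning in the study for many participants. Multimedia Appendix 2 or a full protocol may record prior use, and the Limitations section concedes limits on causal inference in general terms.

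Much of that stands, and it rules out three stronger readings that a reader might infer:

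- That the before period actually runs from CGM-free to fully CGM-exposed. Only the possibility is shown, and the calendar shares above are not exposure.
- That funding covered exactly the eligible population. The funding criteria are only cited, and the study's MDI, "defined as receiving at least 2 doses of prandial insulin per day", also admits fixed-dose combinations.
- That all before-after changes are diluted. Attenuation toward zero applies to continuers only. In discontinuers the contrast changes in kind. Baseline CGM metrics are recorded during wear in everyone, and the primary outcome has no baseline.

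What the reply does not remove is that placing a sensor in everyone does not show that nobody already had one. The article also fixes the continuer contrast and the paired tests without confining them to participants new to CGM. Recording prior use in an appendix would not help unless the analysis used it.

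**Conclusion.** The point holds in conditional form. Prior CGM use was possible for every enrolment date, is not excluded, and does not enter the stated analysis. The continuers' CGM-impact analysis therefore lacks an assured CGM-free baseline for HbA1c and patient-reported outcomes. Any bias there has the form (1-p), and its size cannot be computed because p is not given; at p = 0 there is none.

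For severe hypoglycemia, the look-back may mix CGM-free and CGM-covered time. Full coverage is possible for at most about 27% to 33% of enrolment dates under the dates in Results, assuming even enrolment, and for none if recruitment lasted 6 months from January 2024. Those two recruitment statements must be reconciled. The matter concerns secondary and safety results. It is worth correcting before analysis because the correction is cheap, but it does not threaten the primary estimate.

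**What to change.** - Take the date of first CGM supply for each participant from eCAP or the funded-device record, and classify prior use at visit 0 as none or any.
- Restrict the continuers' CGM-impact analysis to participants with no CGM before visit 0, and show prior users separately.
- Report the HbA1c, patient-reported and severe-hypoglycemia before-after results by prior CGM use.
- Correct whichever recruitment statement is wrong, so that the look-back can be dated.
- If the records show that nobody had prior CGM, state that and leave the analysis unchanged.

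The cost is one retrospective data pull and some analysis wording, with no new visits or participants. The article places formal analysis after the end of follow-up, so this can be settled before results are seen. The price is a smaller sample and slightly wider intervals in the continuer analysis if prior users are found.

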### Hypothesis and Objectives

We hypothesize that approximately 25% of people with T2DM on MDI have sufficient β cell secretory capacity to safely discontinue prandial insulin. In these cases, treatment could be optimized by introducing agents with proven cardio-renal or weight-lowering benefits according to current clinical guidelines.

The main objective is to evaluate a simple personalized medicine protocol in routine clinical practice for people with T2DM on MDI. The protocol, based on clinical and analytical parameters, aims to improve diagnostic accuracy and potentially simplify treatment in this population.

Secondary objectives include describing patient characteristics; conducting detailed phenotyping of pancreatic function and autoimmunity status; and evaluating the impact of the intervention on glycemic control, treatment adherence, and quality of life.

## Methods

This paper reports a study protocol developed in accordance with the SPIRIT (Standard Protocol Items: Recommendations for Interventional Trials) guidelines.

### Study Design and Settings

We designed a nonrandomized pragmatic intervention study targeting people diagnosed with T2DM who were treated with MDI. This before-and-after intervention was designed to assess the real-world applicability of a precision medicine algorithm. Rather than using a control group, this study uses each participant as their own control, comparing clinical outcomes before and after the intervention. The intervention was adapted to be integrated into routine clinical workflows across both primary and specialized care settings.

This study is being conducted within 21 primary health care centers of the Catalan Health Institute (Institut Català de la Salut) in the Lleida health care region (Catalonia, Spain; Multimedia Appendix 1) together with the Department of Endocrinology and Nutrition, University Hospital Arnau de Vilanova, as the reference tertiary center.

### Eligibility Criteria

We included adults aged ≥18 years with a confirmed diagnosis of T2DM. To be enrolled in the study, participants must be on an MDI regimen, defined as receiving at least 2 doses of prandial insulin per day (either regular insulin or a rapid-acting insulin analogue) administered separately or as part of a fixed-dose combination.

We excluded individuals with a known diagnosis of diabetes other than T2DM, pregnant women, and those with severe cognitive impairment or any condition that prevented the use of CGM. We also excluded participants with current drug or alcohol abuse, those receiving systemic glucocorticoids for acute conditions at the time of inclusion, and individuals undergoing temporary insulin therapy expected to last less than 6 months.

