### Data Collection and Management

#### Overview

Data for this study are collected from electronic medical records and patient-reported questionnaires during study visits. Clinical and demographic information, including age, sex, educational level, BMI, diabetes duration, comorbidities, complications, and current pharmacological treatment, is obtained from the eCAP (electronic medical record) software and supplemented by medical interviews. Laboratory variables, including C-peptide, GADAb, HbA_1c_, and estimated glomerular filtration rate, are extracted from recent laboratory reports or requested when unavailable. CGM data, including metrics such as time in range, hypoglycemia episodes, and glucose variability, are downloaded directly from the devices used by participants throughout the study. Patient-reported outcomes, including quality of life, treatment satisfaction, medication adherence, and physical activity, are assessed using validated questionnaires. All study variables and corresponding time points are summarized in Table 1. In addition, detailed information on the study variables, including their definitions and data sources, is provided in Multimedia Appendix 2.

**Table 1. T1:** Study timeline, variables, and procedures.

Data collected	Evaluation time point			
	Preselection	Visit 0—inclusion	Visit 1—intervention (2 weeks)	Visit 2—final follow-up (6 months)
Inclusion and exclusion criteria	✓	✓		
Sociodemographic data^a^		✓		
Anthropometric data^b^		✓		✓
Clinical data^c^		✓		✓
CGM^d^ data			✓	✓
Laboratory data^e^		✓		✓
Smoking status		✓		
Pharmacological treatment^f^		✓		✓
Severe hypoglycemia^g^		✓		✓
Questionnaires^h^		✓		✓

a Age, gender, primary care center, current occupational status, level of education, number of children, date of menopause, and whether the participant is the sole caregiver of another person.

b Weight, height, BMI, and abdominal circumference.

c Arterial hypertension, dyslipidemia, micro- and macrovascular complications, heart failure, and renal disease of any etiology (estimated glomerular filtration rate <60 mL per minute per 1.73 m2).

d CGM: continuous glucose monitoring.

e Inclusion visit: hemoglobin A_1c_ (HbA_1c_), glutamic acid decarboxylase autoantibody, glycemia, and C-peptide; final visit: HbA_1c_.

f Prescription and dosage of diabetes drugs.

g Inclusion visit: last 12 months; final visit: 6 months of study.

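### Entry sets no minimum time already on MDI, so for recent starters the severe-hypoglycemia look-back, and possibly the baseline HbA1c, describes a period before MDI

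*Protocol article*

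**What the plan says.** **Entry.** Under Eligibility Criteria, "participants must be on an MDI regimen, defined as receiving at least 2 doses of prandial insulin per day". This describes treatment at entry. The one criterion that mentions how long insulin lasts excludes "individuals undergoing temporary insulin therapy expected to last less than 6 months", which concerns expected future duration.

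**Comparison.** Study Design and Settings gives up a control group: "this study uses each participant as their own control, comparing clinical outcomes before and after the intervention". Sample Size and Statistical Analysis plans paired tests for change over time.

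**Severe hypoglycemia.** Study Outcomes sets the 6 months after the intervention against the year before: episodes are "compared with the 12-month period before enrollment". Table 1, note g, gives the same windows: "Inclusion visit: last 12 months; final visit: 6 months of study".

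**HbA1c.** Table 1, note e, lists one value at inclusion and one at the end ("glutamic acid decarboxylase autoantibody, glycemia, and C-peptide; final visit: HbA_1c"). The data collection overview lets laboratory values come from an existing recent report and has them requested only when there is none.

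**Treatment history.** Table 1, note f, lists "Prescription and dosage of diabetes drugs". The planned baseline description includes duration of diabetes, not time on MDI. Full variable definitions are in Multimedia Appendix 2, which is not shown.

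**The concern.** An own-control comparison is interpretable only if the earlier period represents the treatment that the intervention is meant to change. Nothing in the entry rules ensures this for outcomes that look backward.

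- **Severe hypoglycemia.** This is the named safety outcome. For a recent starter, most of the look-back was spent on whatever treatment came before MDI. If that carried less risk, the earlier rate is too low and the comparison is tilted towards apparent harm or a hidden benefit. Converting 12-month and 6-month counts to rates corrects the unequal lengths, but not a look-back spent on another treatment.
- **HbA1c.** A value measured soon after starting MDI, or taken from a report that predates the start, may still be about to fall. The paired analysis cannot separate that fall from an effect of the algorithm. Among those who continue MDI, the article assesses the impact of CGM on HbA1c, and the same fall could be read as a CGM effect.

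**Working it through.** **1. The plan's own figure.** With anticipated proportion 0.25, margin 0.05 and a frame of 1388 people:

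- n0 = 1.96² × 0.25 × 0.75 / 0.05² = 288.1
- with finite population correction: 288.1 / (1 + 287.1/1388) = 238.7, rounded up to 239.

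The stated 239 is reproduced and does not depend on time on MDI. It serves below only as the number analysed.

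**2. Share of the look-back before MDI.** The 12-month window is the document's. For m months on MDI at entry, the share is (12 − m)/12.

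| Months on MDI at entry | Share of look-back before MDI |
|---|---|
| 1 | 92% |
| 3 | 75% |
| 6 | 50% |
| 9 | 25% |
| 12 | 0% |

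This step needs no outside assumption.

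**3. Effect on the hypoglycemia comparison (assumed inputs).** Let f be the share of recent starters, s the share of their look-back before MDI, and k the pre-MDI rate relative to the on-MDI rate. With no true effect:

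after/before rate ratio = 1 / [(1 − f) + f × ((1 − s) + s × k)]

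- f = 5%, s = 50%, k = 0.5: 1/0.9875 = 1.01
- f = 10%, s = 75%, k = 0.5: 1/0.9625 = 1.04
- f = 20%, s = 95%, k = 0.25: 1/0.8575 = 1.17

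Over f = 5–20%, s = 50–95% and k = 0.25–0.5, the ratio runs from 1.01 to 1.17, an apparent worsening.

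**4. Effect on the mean HbA1c change (assumed inputs).** If recent starters fall by δ points whatever the algorithm does, the spurious mean fall is f × δ.

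- f = 2%, δ = 0.5: 0.01 points
- f = 10%, δ = 1.0: 0.10 points
- f = 30%, δ = 1.5: 0.45 points

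Assuming also an SD of change of 1.2, the standard error at n = 239 is 1.2/√239 = 0.078. The chance that a paired test reaches two-sided P<.05 with no algorithm effect is then:

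| f | δ | Spurious mean fall | Chance of P<.05 |
|---|---|---|---|
| 2% | 0.5 | 0.01 | about 5% |
| 5% | 0.5 | 0.025 | about 6% |
| 5% | 1.0 | 0.05 | about 10% |
| 5% | 1.5 | 0.075 | about 16% |
| 10% | 1.5 | 0.15 | about 49% |
| 20% | 1.5 | 0.30 | about 97% |

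The result ranges from negligible to decisive, depending on inputs that the document does not give.

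**5. Which other outcomes are exposed.** Baseline CGM is recorded after inclusion: "All participants used CGM for 10 to 15 days prior to the intervention", so it is recorded on MDI. Baseline questionnaires are completed at the inclusion visit, also on MDI. The primary outcome is a single proportion at 6 months with a 95% CI and has no earlier value.

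**The case against.** **Recent starters belong in the study.** The target is people treated with MDI in routine care, and a pragmatic study may properly include them. This stands. It is why the full-sample analyses should remain and no change to eligibility is proposed.

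**Transient cases are already excluded.** Insulin started for a passing deterioration, or for a short glucocorticoid course, falls largely under the temporary-insulin exclusion. This mostly stands; what remains is misjudgement of the expected duration. But the criterion does not address the person who has just begun long-term MDI.

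**The limitations already cover it.** The article says that its limitations may restrict causal inference. It does not mention recent starters, and a general caution does not correct a look-back that can be corrected.

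**This is analysis-plan detail, and the appendix may record time on MDI.** Both are possible. The windows and the entry rule are nevertheless fixed in the article, and if a start date is already recorded the remedy is cheaper.

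**Stronger readings.** A reader might infer that the primary proportion is biased by the missing duration rule. The documents do not support this: there is no before-value, so recent starters can only alter the case mix. A reader might also infer that every natural change is credited to the algorithm. For severe hypoglycemia the distortion tends to run the other way.

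**Conclusion.** The point holds for two secondary comparisons. For severe hypoglycemia it is firm in structure: for anyone on MDI for less than 6 months at entry, more than half of the look-back precedes MDI. The direction, an earlier rate that is too low, rests on the assumption that the previous treatment carried less risk. For HbA1c it is conditional on the baseline value not yet reflecting established MDI.

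The overall size is unknown because the share of recent starters is not given. Under the assumed ranges, the rate ratio is distorted by 1% to 17% and the mean HbA1c change by 0.01 to 0.45 points. The high false-positive rates in the working need both a share of 10% or more and a 1.5-point natural fall. They illustrate what is possible and say nothing about what happened in this trial. Baseline CGM and questionnaires do not describe a period before MDI, and the sample size is unaffected. This is an inexpensive improvement to the secondary and safety analyses, not a defect in the primary one.

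**What to change.** Recruitment closed on March 31, 2025, so act at analysis:

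1. From eCAP, obtain the date on which the current continuous MDI regimen began. A first-ever prandial prescription is not enough, because it could precede an interruption.
2. Analyse severe hypoglycemia as a rate, counting only look-back person-time and events on MDI. If look-back events were not dated, restrict this comparison to participants on MDI for the full 12 months.
3. Keep the full-sample paired HbA1c analysis. Add a sensitivity analysis limited to participants on MDI for at least about 3 months when the baseline HbA1c was measured, using the sample date and not the visit date. Do the same for the CGM question in continuers.
4. Report time on MDI at baseline. Optionally, show the primary proportion by time on MDI as a descriptive sensitivity result.

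**Cost:** one extra date per participant and a few lines in the analysis plan. Record-based start dates may be imperfect, and the restricted analyses lose a little precision. The 239 does not change.
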